#### The influence of chronic combination therapy on proteinuria (Visit 13)

Following completion of study visit 8, subjects will be discharged home to continue both the study drug and lisinopril for three months of long-term therapy (Figure 2). For the final visit of the study, subjects will return after one week of HS diet with a completed 24-hour urine collection, which will be analyzed for protein. The 24-hour urine protein measured at this visit will be compared using repeated measures analyses to the urine protein levels obtained from 24-hour urine collections completed at each inpatient visit on HS dietary balance (visits 3, 6, 8). *Anticipated Results:* Combination therapy (calcitriol + lisinopril) will additively or synergistically lower proteinuria when compared to placebo + lisinopril, thereby paralleling prior animal studies that showed that the combination of VDR agonist + conventional RAS inhibitor therapy induced synergistic renoprotective benefits in mouse models of diabetes [19-21].

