**Figure 2 F2:**
[figure not shown]
***VALIDATE-D study schema*****: subjects will be screened and then may undergo a medication washout to withdraw interfering anti-hypertensive medications (when applicable).** Aim 1: The *circulating* RAS will be assessed on LS diet before and after randomization to calcitriol/placebo (visits 2 & 5). Aim 2: The *renal-vascular tissue-RAS* will be assessed on HS diet before and after calcitriol/placebo (visits 3 & 6). Aim 3: All subjects will then receive lisinopril 5 mg/d in addition to calcitriol/placebo to assess the impact of combination therapy (calcitriol + lisinopril vs. placebo + lisinopril) on the renal-vascular tissue-RAS (visits 6 & 8) and proteinuria (visits 6, 8, 13). Serum calcium and phosphate will be monitored weekly throughout the study for safety, at each visit and at designated safety checks (visits 4, 7, 9–12).

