### Renal-vascular tissue-RAS on HS diet (Visit 6)

After a third week on the study drug, subjects will return on HS diet for an overnight CRC study visit 6, that is identical to Visit 3. This visit will permit assessment of study Aim 2 (to assess whether direct VDR activation lowers renal-vascular tissue-RAS activity in human diabetes) by comparing the renal-vascular tissue-RAS activity before and after calcitriol/placebo. *Anticipated Results:* It is anticipated that calcitriol therapy will raise basal RPF and increase the RPF sensitivity to angiotensin II, thereby demonstrating that VDR activation improves renal-vascular hemodynamics by lowering local renal-vascular RAS activity in human diabetics without CKD.

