#### The influence of combination VDR-agonist and ACE inhibitor therapy on the renal-vascular tissue RAS (Visit 8)

Upon completing study visit 6, all subjects will receive lisinopril (initially 2.5 mg daily, which will be increased to 5 mg daily after one week, unless blood pressures are below 90/50 mmHg or subjects experience orthostatic symptoms) in addition to their randomized study drug (Figure 2). After 2 weeks of daily combined therapy (calictirol + lisinopril or placebo + lisinopril), subjects will return on the HS diet for a final inpatient CRC visit that is identical to study visits 3 & 6. Comparing the outcomes of study visits 6 and 8 will permit evaluation of Aim 3 of this study (to assess whether direct VDR activation in combination with ACE inhibition exerts an additive or synergistic effect on the renal-vascular tissue-RAS and proteinuria). *Anticipated Results:* Combination therapy (calcitriol + lisinopril) will additively or synergistically raise RPF and increase the RPF sensitivity to angioensin II infusion, reflecting decreased renal-vascular tissue-RAS activity when compared to placebo + lisinopril.

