At least three unique findings will emerge from the VALIDATE-D study. First, this intervention study will conclusively evaluate whether vitamin D therapy lowers the *circulating* human RAS. By using direct VDR agonists and a meticulous study design to account for confounders of the RAS (diet, posture, medications, time of day), this study will investigate whether calcitriol therapy lowers the maximally stimulated RAS on a LS diet in comparison to placebo. Second, this study will evaluate whether direct VDR activation improves renal-vascular hemodynamics by increasing renal blood flow and the renal-vascular sensitivity to angiotensin II; both of these observations are consistent with reductions in the renal-vascular tissue-RAS as would be induced by an ACE inhibitor. The study design includes a comparison of renal-vascular hemodynamics (while the circulating RAS is suppressed on a HS diet) during treatment with calcitriol vs. placebo, and then again during treatment with calcitriol + lisinopril vs. placebo + lisinopril (Figure 2). In this regard, the study design is optimized to decipher the individual role of VDR activation, and the effect of combining VDR activation with conventional RAS inhibition, since this combination therapy has been shown to provide synergistic renoprotection in animal models of diabetes [19-21]. The assessment of the renal-vascular tissue-RAS in humans is a unique and defining aspect of this study protocol. The renal vasculature is specifically sensitive to the effects of angiotensin II, and the magnitude of renal-vascular responses to angiotensin II is inversely proportional to the degree of local tissue-RAS activity [5,11,16]. High endogenous tissue-RAS activity results in a blunted local sensitivity to the effect of angiotensin II, while inhibiting the local renal-vascular tissue-RAS (for example with an ACE inhibitor) improves the renal-vascular sensitivity to angiotensin II [30] (Figure 3). Therefore, our ability to measure renal hemodynamics via *para*-aminohippurate clearance permits us to objectively ascertain the state of the renal-vascular tissue-RAS in response to drug intervention (calcitriol, lisinopril, placebo) and in response to provocation by angiotensin II. Lowering renal-vascular tissue-RAS activity in pathologic states such as diabetes and obesity with conventional pharmacotherapy (ACE inhibitor or angiotensin receptor blocker) has shown efficacy for the primary prevention of diabetic nephropathy [15,40,41]. Thirdly, the impact of adding chronic VDR-agonist therapy to ACE inhibitor therapy on proteinuria will be assessed. Since the study population is strategically selected to have diabetes without CKD, together these study findings will have implications for recommending vitamin D supplementation to lower unfavorable RAS activity for the *primary prevention* of diabetic nephropathy.

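### For proteinuria, the Visit 13 comparison can show an add-on effect of calcitriol in subjects taking lisinopril, but cannot tell an additive from a synergistic or sub-additive combination

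*Protocol article*

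**What the plan says.** Aim 3 of the protocol article (Background, and again in the section on Visit 8) asks whether calcitriol combined with an ACE inhibitor acts additively or synergistically on the renal-vascular tissue-RAS and on proteinuria. The Figure 2 legend assigns to this aim the tissue-RAS at Visits 6 and 8 "and proteinuria (visits 6, 8, 13").

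The sequence of treatment is:

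- Visit 6: "After a third week on the study drug, subjects will return on HS diet for an overnight CRC study visit 6".
- Between Visits 6 and 8: "Upon completing study visit 6, all subjects will receive lisinopril", on top of the randomised study drug.
- Visit 8: "After 2 weeks of daily combined therapy".
- Visit 13: after Visit 8, subjects "continue both the study drug and lisinopril for three months of long-term therapy".

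The Visit 13 section compares 24-hour urine protein with the values from Visits 3, 6 and 8 by repeated measures. The Outcomes section adds unpaired comparisons of changes between the calcitriol and placebo groups. The anticipated result is that calcitriol + lisinopril "will additively or synergistically lower proteinuria when compared to placebo + lisinopril", and the article likens this to the synergy seen in mouse models.

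**The concern.** Whether two drugs combine additively or synergistically is a question about interaction. Answering it requires calcitriol's effect without lisinopril and its effect with lisinopril, at the same duration of calcitriol. In this design both change together: calcitriol has been taken alone for 3 weeks when lisinopril starts, and for about 18 weeks when proteinuria is finally measured. No group stays on calcitriol alone or on placebo alone after Visit 6.

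At stake is what the trial may conclude. A significant result could be reported as synergy, in parallel with the animal work, when it came only from longer calcitriol exposure. It could equally be reported as additive or synergistic when the combination was less than additive. No detail in an analysis plan can supply the missing 18-week values.

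**Working it through.** **1. Exposure times.** From the sections on Visits 6, 8 and 13, taking three months as about 13 weeks:

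| Visit | Weeks of study drug | Weeks of lisinopril |
|---|---|---|
| 6 | 3 | 0 |
| 8 | 3 + 2 = 5 | 2 |
| 13 | 5 + 13 = about 18 | 2 + 13 = about 15 |

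The abstract's 3.5 months of lisinopril follow-up is 3.5 × 365.25 / 12 / 7 = 15.2 weeks, which agrees. Depending on how months are converted, study-drug exposure at Visit 13 is 17.0 to 18.2 weeks.

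**2. What each contrast estimates.** Let C(t) be calcitriol's own effect after t weeks without lisinopril, and I the interaction with lisinopril at Visit 13. Randomisation and the common lisinopril schedule remove shared time trends and lisinopril's own effect.

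- Between-arm difference at Visit 6: C(3).
- Between-arm difference at Visit 13, raw or relative to Visit 3: C(18) + I.
- Between-arm difference in change from Visit 6 to Visit 13: I + [C(18) − C(3)].

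C(18) is never observed. The third contrast cannot separate I from growth in C. The second is non-zero under synergy (I adds to C), under additivity (I = 0), and under sub-additivity. If half of the calcitriol effect is lost, I = −C(18)/2 and the contrast is C(18)/2.

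**3. Visit 8.** The same mixing occurs from Visit 6 to Visit 8, but over 3 to 5 weeks only. With the illustrative curve C(t) = Cmax × (1 − exp(−t/τ)):

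| τ (weeks, assumed) | [C(5) − C(3)] / Cmax | [C(18) − C(3)] / Cmax |
|---|---|---|
| 1 | 4% | 5% |
| 4 | 19% | 46% |
| 8 | 15% | 58% |
| 16 | 10% | 50% |

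**4. How often the change contrast is significant with no interaction.** The plan's only computed sample size concerns plasma renin activity. No effect, SD or correlation is given for proteinuria, so everything from here on is assumed except 20 per arm and two-sided 0.05. Work in SD units of (log) urine protein, with between-visit correlation ρ. The SD of a change is √(2(1 − ρ)), which is 1.00 for ρ = 0.5 and 0.77 for ρ = 0.7. For growth g = C(18) − C(3), the t-test (38 df) has non-centrality g / (SD of change × √(2/20)). For g = 0.75 and ρ = 0.5 this is 0.75 / 0.316 = 2.37.

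| Growth g (SD) | ρ = 0.5 | ρ = 0.7 |
|---|---|---|
| 0 | 5% | 5% |
| 0.25 | 12% | 17% |
| 0.5 | 34% | 51% |
| 0.75 | 64% | 85% |
| 1.0 | 87% | 98% |

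A second parameterisation combines the exponential curve with an SD of log change from 0.3 to 0.7. For τ of 4 to 16 weeks it gives 10% to 45% with Cmax = 0.3, and 18% to 87% with Cmax = 0.5. For τ = 1 week it gives 5% to 6%.

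**5. The plain Visit 13 difference under a sub-additive combination.** If lisinopril halves a calcitriol-alone effect of 0.8, 1.2 or 1.6 SD, the remaining difference is 0.4, 0.6 or 0.8 SD. The Visit 13 t-test then rejects about 23%, 46% or 69% of the time.

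**The case against.** The strongest reply is that the Visit 13 comparison is randomised and blinded, with equal lisinopril duration in both arms, so it validly shows added benefit. That stands. A reader might infer from the lack of an 18-week calcitriol-only group that the proteinuria comparison is invalid or biased. The documents do not support this: in the ordinary sense of benefit on top of lisinopril, the comparison answers its question. A slow calcitriol effect that persists on lisinopril is itself such a benefit.

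Next, the article says additive *or* synergistic. If the truth is strictly additive, that either-or statement is true, so the rates in step 4 are not errors against it. They are errors only if the result is reported as synergy. The article names no Visit 6-to-13 interaction test and no rule for declaring synergy; the nearest it comes is the animal parallel in an anticipated result. This also stands, and limits the rates to illustrating a risk of interpretation. It does not rescue the either-or statement, which a sub-additive combination would make false while the Visit 13 difference could still be significant.

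A slow effect is also not established. The Discussion suggests that direct VDR agonists may act sooner than vitamin D3, and Visit 8 offers a proteinuria contrast with much less confounding. Both points are fair, but neither yields an estimate of C(18).

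Finally, a reader might cite the Discussion's statement that "the study design is optimized to decipher the individual role of VDR activation" as a claim about proteinuria. In context it follows a sentence on renal-vascular hemodynamics, which are measured at Visits 3, 6 and 8. Its calcitriol-alone data are already the 3-week data, and it needs no change on this account.

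**Conclusion.** The point holds as a limit on interpretation. At Visit 13 the trial can estimate the add-on effect of about 18 weeks of calcitriol in subjects taking lisinopril. It cannot establish that the drugs' effects on proteinuria are additive, nor separate that from synergy or sub-additivity. This follows from the visit schedule alone and needs no assumed number.

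How often it would mislead is unknown. With no interaction and 20 per arm, the chance of a significant change contrast that would be misread as synergy runs from about 5%, if calcitriol's effect is complete by 3 weeks, to 64% or more if it grows by 0.75 SD or more. These figures rest on assumed effect sizes, time courses and correlations, and on the Visit 6-to-13 change being the contrast used. The article fixes none of these.

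**What to change.** In the Visit 13 section, and in Aim 3 as it applies to proteinuria:

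1. State the target as the between-arm difference in urine protein at Visit 13 relative to pre-randomisation Visit 3, that is, the add-on effect of about 18 weeks of calcitriol in subjects taking lisinopril. The Discussion already frames its third finding this way, as the impact of adding chronic VDR-agonist therapy to an ACE inhibitor.
2. Remove the words on additive or synergistic lowering from the proteinuria conclusion.
3. State that between-arm changes from Visit 6 to Visit 13 mix interaction with duration of calcitriol and will not be read as synergy.

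The cost is wording and a choice of contrast, with no new visits, samples or subjects. The synergy claim for proteinuria is given up. Testing it would need concurrent groups without lisinopril followed for the same time, which is a different trial and is not proposed here.

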### Safety & monitoring

#### Calcium/Phosphate

To minimize the risk of hypercalcemia due to calcitriol, all subjects will undergo laboratory evaluation of serum calcium and phosphate at 1–3 week intervals throughout the study duration, including at the aforementioned study visits and additionally at designated safety visits (visits 4, 7, 9–12). If calcium or phosphate rises above the upper limit of normal, the test will be repeated in 3 days and subjects will be counseled by our dedicated study dietician on adherence to a low calcium diet (Dietary Calcium Intake Recommendations Additional file 1). If calcium or phosphate levels remain elevated, or the calcium-phosphate product exceeds 50, the dose of study drug will be reduced by one third. Based on several prior studies that have employed chronic VDR-agonist therapy in combination with lowered dietary calcium intake, our dosing and study duration are unlikely to invoke hypercalcemia or hyperphosphatemia [27-29].

#### Blood pressure

During PAH and angiotensin II infusion, blood pressure (BP) will be monitored every 2 minutes using an automated sphyngomanometer. An increase in BP is an expected effect of angiotensin II infusion, and the following protocol has been used safely in over 1500 subjects [5]. The 0.3 ng/kg/min dose was selected because it does not induce a pressor effect but still influences renal-vascular hemodynamics [30], and the 1 ng/kg/min dose was selected because it has previously been shown to induce minimal BP elevations well within a safety range [5,30]. A study physician will supervise all angiotensin II infusions as previously described [5].

All subjects will monitor their BP daily with a home sphygmomanometer while on the washout phase (when applicable) and while on lisinopril and will communicate their readings to study staff twice weekly. Study staff will monitor for unsafe high BP during the washout period (>159/99 mmHg) or unsafe hypotension during lisinopril treatment (<90/50 mmHg). Subjects who develop high BPs during the washout period may be treated with amlodipine which has a neutral effect on RAS components. Subjects who develop low BPs on lisinopril may have their dose reduced 50%, however, if a 2.5 mg daily dose is not tolerated, subjects will be removed from the study.

#### Blood glucose

Subjects will be asked to check their home blood glucose daily, and study staff will monitor their glycemic control throughout the study. If fasting morning blood glucose is consistently >150 mg/dL, medications will be adjusted by a study physician. Such adjustments include increasing the dose of a home medication or adding a second oral hypoglycemic agent.

#### Lipids

Any subject who has a screening LDL cholesterol greater than 100 mg/dL, will either be prescribed simvastatin 20-40 mg daily, or if already taking a statin medication, have their pre-existing statin dose increased, to remain consistent with clinical standards of care for diabetes.

### Laboratory measurements

25(OH)D (Diasorin, Inc., Stillwater, MN), 1,25(OH)_2_D (Diasorin), parathyroid hormone (Beckman Coulter, Fullerton, CA), and serum and urine electrolytes (including calcium and phosphate) will be measured at baseline at all visits. Components of the circulating RAS, including plasma renin activity (Diasorin) and aldosterone (Siemens, Los Angeles, CA), will be measured from samples drawn in upright and supine posture (Visits 2, 5, 13) and before and during angiotensin II infusion (Visits 3, 6, 8) [5]. For assessment of RPF, *para*-aminohippurate will be measured in triplicate at steady-state and during angiotensin II infusion and will then be adjusted by body surface area in all RPF calculations (Visits 3, 6, 8).

### Statistical analyses

#### Sample size calculations

Sample size calculations were made using our prior data evaluating the impact of vitamin D on the systemic [23] and renal-vascular tissue-RAS [5] by paired analyses with an alpha-error of 0.05. For Aim 1, prior data suggest that therapy with a VDR agonist could reduce plasma renin activity, a measure of the circulating RAS, by 1 ng/mL/hr (SD = 0.54). A minimum of 5 subjects would be required in each study arm for a paired comparison to detect this difference with a power of 0.9. In our pilot intervention study, we demonstrated an effect of vitamin D therapy on the renal-vascular tissue-RAS (Aims 2 & 3) in a sample of 14 subjects. To account for underestimation of sample-size, variability in measurements, and to permit non-paired comparisons, we intend to study 20 subjects in each intervention group.

#### Outcomes

Paired and repeated measures analyses will be used to evaluate intra-individual changes in the circulating RAS, RPF responses to angiotensin II infusion (i.e. renal-vascular tissue-RAS), and urine protein levels. Non-paired comparisons will be used to evaluate changes in these parameters between the calcitriol and placebo groups. A two-tailed *P*-value < 0.05 will be considered statistically significant.

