### Circulating RAS on LS diet (Visit 2)

Study visit 2 is designed to measure the baseline circulating RAS under conditions designed to induce maximal stimulation of the circulating RAS: restricted dietary sodium intake and upright posture. After one week of LS diet consumption, subjects are studied at 8 AM in the morning (Figure 2). Subjects will maintain an upright standing posture for at least 1 hour. Blood samples are obtained at the end of the postural phase to measure circulating RAS components (plasma renin activity, angiotensn II, aldosterone).

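### The between-arm comparisons of change do not adjust for the baseline values that the trial collects; this is valid but gives up precision in a 40-subject trial

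*Protocol article*

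**What the plan says.** The Outcomes section separates two kinds of analysis. Within subjects: "Paired and repeated measures analyses will be used to evaluate intra-individual changes in the circulating RAS", with RPF responses and urine protein in the same sentence. Between arms: "Non-paired comparisons will be used to evaluate changes in these parameters between the calcitriol and placebo groups". The threshold is two-sided: "A two-tailed *P*-value < 0.05 will be considered statistically significant".

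The Sample size section supports the same reading. Its calculation was made "by paired analyses with an alpha-error of 0.05", and the sample was then enlarged, among other reasons, "to permit non-paired comparisons, we intend to study 20 subjects in each intervention group".

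The baseline values exist. Under the heading for Visit 2: "Study visit 2 is designed to measure the baseline circulating RAS". The Visit 3 section describes the baseline RPF response to angiotensin II, and the section on chronic combination therapy lists a 24-hour urine protein at Visit 3. Randomisation follows Visit 3. Visit 5 repeats Visit 2, and Visits 6 and 8 repeat Visit 3. That same section plans a repeated-measures analysis of urine protein over Visits 3, 6, 8 and 13 without giving a model. The article nowhere mentions adjustment for baseline.

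**The concern.** A comparison of changes subtracts the whole baseline value from the follow-up value, which fixes the baseline slope at 1. When the correlation between baseline and follow-up is below 1, this subtracts too much and adds the noise of the baseline to the outcome. ANCOVA estimates the slope from the same data. In a randomised trial it targets the same treatment difference with a smaller variance, except when the correlation is very high.

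With 20 per arm, precision limits what Aims 2 and 3 can show. The article gives no effect size or SD for RPF response or urine protein, only a pilot of 14 subjects, so no margin is documented for those endpoints.

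**Working it through.** **Inputs from the article.** Plasma renin activity: "could reduce plasma renin activity, a measure of the circulating RAS, by 1 ng/mL/hr (SD = 0.54"), read here as the SD of the within-subject change. Alpha 0.05, two-sided. Power 0.9. 20 per arm.

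**Input assumed.** The correlation rho between baseline and follow-up is not given, so it is varied from 0.3 to 0.9. Equal variance at both times is also assumed.

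**Step 1: the article's own figure.** It states: "A minimum of 5 subjects would be required in each study arm for a paired comparison to detect this difference with a power of 0.9".
- Normal approximation: n = ((1.960 + 1.282) × 0.54 / 1)² = 3.06.
- Small-sample term: 1.960² / 2 = 1.92. The sum is 4.98, so n = 5, as stated.
- The exact two-sided paired t-test has power 0.866 at n = 5 and 0.947 at n = 6. The difference has no consequence, since 20 per arm are planned.

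**Step 2: what the planned between-arm comparison can detect.** The standard error of a difference in mean change is SD × √(2/20) = 0.316 SD.
- By the noncentral t with 38 degrees of freedom, 80% power is reached at 0.91 SD of change. For plasma renin activity that is 0.91 × 0.54 = 0.49 ng/mL/hr.
- At the assumed effect of 1 ng/mL/hr the power is above 99.9%. If 0.54 were instead the SD at a single visit with rho = 0, the SD of change would be 0.54 × √2 = 0.76, and the power would still be about 98%.

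**Step 3: variance with and without adjustment.** With σ² the variance at one visit:
- Change score: 2σ²(1 − rho).
- ANCOVA: σ²(1 − rho²).
- Ratio: (1 + rho)/2, multiplied by about 1 + 1/36 for estimating one covariate with 40 subjects.

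The last two columns give the number of subjects that a change-score analysis would need for equal precision, and the ANCOVA power for an effect that has 80% power by change scores.

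| Assumed rho | (1 + rho)/2 | With covariate cost | Variance reduction | 40 subjects worth about | ANCOVA power |
|---|---|---|---|---|---|
| 0.3 | 0.65 | 0.67 | 33% | 60 | 93% |
| 0.5 | 0.75 | 0.77 | 23% | 52 | 89% |
| 0.7 | 0.85 | 0.87 | 13% | 46 | 85% |
| 0.9 | 0.95 | 0.98 | 2% | 41 | 81% |

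**Step 4: where the gain ends.** Setting (1 + rho)/2 × 37/36 = 1 gives rho = 72/37 − 1 = 0.946. Adjustment gains for any correlation below about 0.95.

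**The case against.** - **The planned method is not wrong.** An unpaired comparison of changes is valid under randomisation. A reader might infer that chance baseline imbalance biases the result. With 20 per arm, an imbalance of 0.3 SD or more arises about 34% of the time (0.3/0.316 = 0.95 standard errors). At rho 0.5 an imbalance of 0.3 SD shifts the change-score estimate by 0.5 × 0.3 = 0.15 SD. That shift is conditional on the imbalance observed, and the standard error of the change score already includes it. It is the same inefficiency seen from another side, not a further defect.
- **An analysis plan may add covariates.** That is possible. The article does more than leave the method open, however: it names the type of between-arm comparison and sizes the trial partly for it. A stated method can be reviewed.
- **The text does not say raw changes.** This is correct. It names no t-test and does not say whether changes are absolute, percentage or on a log scale. The point requires only that no baseline adjustment is stated. Nothing in the text supports a demand for log transformation, and none is made here.
- **Urine protein may already be covered.** The planned repeated-measures analysis could use the baseline efficiently. Its model is not given, so it cannot be said that protein is compared by changes alone.
- **No harm is shown where figures exist.** This stands for plasma renin activity. The tight control of diet, posture, time of day and medication could also make rho high and the gain small.
- **Adjusting Visit 8 for Visit 3 alters Aim 3.** It would if it replaced the planned contrast. The article evaluates Aim 3 from Visits 6 and 8, the increment after lisinopril. Adjusting for Visit 3 estimates the total randomised difference on combination therapy and does not by itself address additivity or synergy. Both are needed.

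**Conclusion.** The point holds as a loss of efficiency that can be avoided, not as an error or a bias. The stated between-arm method leaves the collected baseline values unused as covariates. The cost is about 33% to 13% of the variance for assumed correlations of 0.3 to 0.7, and almost nothing at 0.9. These sizes rest on a correlation that the article does not report and on equal variances at baseline and follow-up.

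A reader might infer that the trial is underpowered because of this choice. The article does not support that. For plasma renin activity, the only endpoint with figures, power is ample either way. For RPF response and urine protein the practical loss cannot be quantified, because no effect size or SD is given; these are the endpoints for which the added precision is most useful.

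**What to change.** Replace the between-arm sentence in Outcomes, before unblinding, with a statement on these lines: differences between calcitriol and placebo will be estimated by ANCOVA, or by a repeated-measures model, with the pre-randomisation value as a covariate. The covariates are:
- Circulating RAS at Visit 5: the Visit 2 value.
- RPF response at Visit 6: the Visit 3 value.
- Urine protein in the repeated-measures analysis already planned: the Visit 3 value.
- RPF response at Visit 8, for the randomised comparison of calcitriol + lisinopril with placebo + lisinopril: the Visit 3 value, not the post-randomisation Visit 6 value.

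Keep the Visit 6 to Visit 8 contrast as a separate Aim 3 analysis, and say that it addresses a different question from the total randomised difference at Visit 8.

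The cost is a few lines of analysis text and one degree of freedom per model (37 instead of 38 in the ANCOVA). No visit, measurement or subject is added.
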